**Evaluating a Novel Approach to Diabetes Management in**

**Zuni Indians**

**Research Protocol**

**June – Dec 2012**

## Abstract

**Purpose:** One in three people will be diagnosed with diabetes by 2050, and the proportion will likely be higher among Native Americans. Diabetes control is currently suboptimal in underserved populations such as Zuni Indians despite a plethora of new therapies. Patient empowerment is a key determinant of diabetes control, but such empowerment can be difficult to achieve due to resource limitation and cultural, language and health literacy barriers. We will conduct a home-based chronic disease (diabetes) educational intervention using Community Health Representatives (CHRs) to associate improvement in Patient Activation Measures scores (primary outcome) and clinical indicators of diabetes control (secondary outcomes).

| Condition                                                                                                                       | Intervention                                                  |
|---------------------------------------------------------------------------------------------------------------------------------|---------------------------------------------------------------|
| The study focus is on lifestyle changes and patient Activation in Diabetic Patients by regular monthly visit by the CHRs | Educational intervention of Lifestyle and patient activation. |

**Study type:** Observational

**Study Design:** Cohort, Prospective

**Biospecimens Retention:** NONE

**Primary Outcome Measure:**

- Patient Activation (time -6 months of education) (No safety issue)  
The Patient Activation Measure (PAM) instrument completed by participants using the short form PAM questionnaire. The response options for the 13 questions use a categorical agreement scale with 4 response options: (i) strongly disagree, (ii) disagree, (iii) agree, (iv) strongly agree, and N/A. The raw score is calculated by adding responses to the 13 questions. If all questions are answered (i.e., no "N/A" is used), the range of raw scores would be 13 to 52. If there is at least 1 item with a response of N/A, the total score will be divided by the number of items completed and multiplied by 13 to yield a normalized raw score. All study procedures were repeated 6-months later, following the intervention.

**Secondary Outcome Measures:**

- Diabetes associated health indicators including HbA1c, Glucose, Lipids, BMI (time -6 months of education) (No safety issue)

**Enrollment:** 60 (both men and women)

Study start date: June 2012

**Study completion date:** December 2012

**Number of arms:** 1

**Eligibility:** All participants are Zuni Natives living in Zuni Pueblo, New Mexico. They are all diabetics with HbA1c level of 6.6% and above in the age range of 21 years to 75 years old.

**Sampling Method:** Non-probability samples recruited directly from the list of previous study conducted at Zuni.

**Summary Description:** The number of American Indians and Alaska Natives (AI/ANs) who have diabetes is growing rapidly, especially among young people. At more than 16%, AI/ANs have the highest age-adjusted prevalence of diabetes among all U.S. racial and ethnic groups. One such population is the Zuni Pueblo home to a small, geographically isolated tribe located in a rural portion of New Mexico, USA. It is home to ~11,000 Zuni Indians and over 90% of all Zunis live in the Pueblo. This socioeconomically disadvantaged population faces a major public health challenge from growing health disparities. Changing lifestyles have led to decreased physical activity and increased caloric intake with high consumption of fast food, soda pop and alcohol. Therefore, the Zuni are experiencing interrelated epidemics of obesity, diabetes, hypertension, kidney disease and intermediate phenotypes.

As part of the Zuni Health Initiative (ZHI), we surveyed participants regarding barriers to healthcare, with particular attention to diabetes care. In ZHI we also collected and stored clinical phenotype information and anthropological measurements from all participants. Participants identified the following barriers: access to care, language barriers, limited patient education, and anxiety around diagnosis, fear of chronic disease, reluctance to participate in self-care, resistance to dietary change, and reluctance to engage in regular exercise. We have previously documented suboptimal glycemic control with a high burden of kidney disease among the Zuni. The burden presented by these barriers ultimately translates into a lack of patient activation and engagement in their healthcare, effectively hindering adoption of healthy behaviors. Focus groups subsequently identified common solutions to overcome some of these barriers, including home-based care, point of care testing, individualized exercise and nutrition prescriptions, and care providers with knowledge of the Zuni language, community and culture.

The information gathered during these focus groups is used to design and implement a Zuni culture specific educational intervention in diabetes. We have devised an innovative educational intervention based on the coordination of four key elements: (a) delivering healthcare that incorporated collaborative communication within the healthcare team and emphasized greater autonomy in care, adherence to the medical regimen, and patient-centered goal setting, all while retaining the ability to address the needs of patients, family members, the healthcare team, and/or the healthcare system; (b) providing innovative educational and organizational approaches, as well as behavior change strategies, that enhanced adherence; (c) addressing health beliefs that reduced adherence by over- or under-predicting maladaptive thoughts (e.g., catastrophizing, minimizing, cognitive dissonance, invincibility, or fatalism) or that interfered with weight control; and (d) using technology to address barriers to achieving desired health outcomes.

Sixty participants with type 2 diabetes (T2D) completed a baseline evaluation including physical exam, Point of Care (POC) testing, and the Patient Activation Measure (PAM) survey. Participants then underwent a one hour group didactic session led by Community Health Representatives (CHRs) who subsequently carried out monthly home-based educational interventions to encourage healthy lifestyles, including diet, exercise, and alcohol and cigarette avoidance until follow up at 6 months, when clinical phenotyping and the PAM survey were repeated

## Background and Rationale

### Obesity and Diabetes: A Global Epidemic

Obesity, a 21st-century medical scourge to which many providers have become desensitized, currently afflicts over 300 million individuals worldwide. While 68% of the American population is considered overweight, our prevalence of overt obesity has skyrocketed to 30% since 1970. Despite being an inherently pathophysiological state, obesity often translates into a higher risk for severe cardiovascular disease such as hyperlipidemia, myocardial infarction, stroke, hypertension, and type 2 diabetes mellitus (T2DM). In turn, worldwide obesity-related healthcare costs are estimated to exceed \$215 billion—and continue to rise exponentially.

Similarly, type II diabetes exacts a steep toll on the American medico-economic climate. Based on the National Health and Nutrition Examination Survey (NHANES) in 2007, the estimated prevalence of diabetes in America surpasses 7.8% of the general population and represents over 23.6 million people. Almost 1 in 5 Native Americans with primary providers from Indian Health Services are diabetic. Resulting medical costs from downstream medical complications such as coronary heart disease, stroke, nephropathy, neuropathy, and dialysis treatment exceed \$174 billion.

Unfortunately, Native American populations bear a disproportionate burden of both obesity and diabetes, compared to all other US populations; 40.1% of American Indian men are obese, in contrast with African-American (26.5%), Hispanic (26.6%), and Asian (2.7%) men. Roughly 16.5% of the total American Indian population has been diagnosed with diabetes, compared to American non-

Hispanic white (6.5%), Asian-American (7.5%), Hispanic (10.4%), and African-American (11.8%) populations.

## **Zuni Indian Population**

Situated in rural, western New Mexico, the Zuni Pueblo is comprised of approximately 11,000 Zuni Indians. Largely endogamous, Zunis tend to value and cultivate multigenerational families, reinforced by low emigration; only 20% live outside the pueblo. Most pueblo members derive income through home-based crafts (e.g. jewelry, fetishes), but the pueblo's socioeconomic status is progressively deteriorating. In turn, most pueblo residents face enormous health care disparities. Moreover, lifestyle shifts during the past century have involved declining physical activity, and increasing intake of high-calorie foods.

Given this socioeconomic and behavioral climate, it comes as no surprise that the Zuni now suffer from a “perfect storm” including a high prevalence of obesity, diabetes, kidney disease, hypertension, and dyslipidemia. Historically, interventions for high-risk populations like the Zunis have been relatively unsuccessful; confounding effects of cultural, historical, and economic barriers not only undermine clinical compliance, but also discourage utilization of available health care services.

## **Health Disparities Among Zuni Indians**

Within the healthcare context, disparity usually refers to the experience of adverse health outcomes by patients who are considered minorities. Health care disparity occurs among a broad backdrop of socioeconomic inequality, but can also be exacerbated by internal factors within the health care delivery system.

Tragically, American Indians (particularly Zuni's) have a lower health status when contrasted with nearly all other U.S. racial or ethnic populations; they experience a disproportionate disease burden, underutilize healthcare services, and their average life expectancy falls 2.4 years short of the

national average. An IHS report identifies low education, high poverty, health care discrimination, and cultural factors as culprits.

Chronic disease hits harder in Zuni. IHS data reveal a mortality rate for obesity and T2DM 2.9 times higher in American Indians, versus the American population. Further health disparity exists in addressing metabolic syndrome, chronic kidney disease, and cardiovascular disease. Whereas Native Americans' chronic disease-related mortality is high, their disproportionate medical burden increasingly burdens the IHS budget and raises healthcare costs.

### **Disparities in Chronic Diseases Among American Indians**

As proposed by the International Diabetes Federation in 2006, “metabolic syndrome” refers to a chronic condition characterized by comorbid metabolic risk factors for T2DM and cardiovascular disease; namely, increased waist circumference, as well as any pair of the following: 1) high serum triglyceride levels ( $\geq 150$  mg/dL); 2) low HDL cholesterol ( $< 50$  mg/dL in women,  $< 40$  mg/dL in men); 3) high blood pressure ( $> 130$  mmHg systolic, or  $> 85$  mmHg diastolic, or undergoing treatment for hypertension); 4) increased free plasma glucose (or history of T2DM). The “medicalization” of this symptom constellation underscores its severity. Once identified, patients must undergo dramatic lifestyle modification focusing on weight reduction and physical activity; otherwise, they are at high relative risk for developing type 2 diabetes, cardiovascular disease, or other associated conditions such as chronic kidney disease, polycystic ovary syndrome, fatty liver disease, or hepatocarcinoma.

In 2008, the population-based, longitudinal Strong Heart Study determined that metabolic syndrome afflicted 38% of all American Indians in the United States. This study further demonstrated that obesity rates in American Indians (AI/AN) exceed the national average. Overweight and obesity in the AI/AN population exceeds the rates for all other U.S. ethnic groups combined. Perhaps most frightening is the trend of increasing overweight and obesity in not only adults, but school-aged

children as well; AI/AN children are at 104% greater risk for being overweight versus non-AI/AN counterparts.

Likewise, T2DM affects the U.S. AI/AN population tremendously. CDC data confirms an over-two-fold relative prevalence of T2DM in AI/AN adult versus the national average. This statistic continues to climb; in the decade preceding 2004, T2DM prevalence in AI/ANs more than doubled. In particular, AI/AN children have experienced a marked rise in T2DM prevalence. Among Pima Indians, whose T2DM rates are documented as the highest world-wide, saw a near-doubling in diagnosis of children from 1990 to 1998. Naturally, the rising number of AI/AN diabetics has led to an upsurge of diabetic complications within Native American communities.

## **Contributing Factors to Health Disparities**

### **Diet**

Historically, unemployment and poverty among AI/ANs has engendered a reliance on federal commodity programs, but these programs often fall short of nutritional requirements. With a paucity of healthy options in tribal grocery stores, Tribal-residing AI-ANs often fall prey to ever-expanding “fast-food” chains around reservations, ingesting diets that are high-calorie, high-fat, and high-sugar. Navajo Reservation grocery stores routinely offer produce in poor condition, and rarely sell low-fat products. Furthermore, the population’s limited demand of perishable produce has dis-incentivized grocers from selling it at an affordable price, and in reasonable volume.

### **Socioeconomic Factors**

Regardless of region, all low-income and ethnic minority American populations with a high prevalence of obesity are more likely to have economic stress, scarcer venues for exercising, less access to reasonably-priced healthy food, and saturation by advertising of calorie-rich foods. Recent

consensus suggests that, in America, disparities in overweight/obese prevalence occur primarily because of varying socioeconomic status.

The Native American socioeconomic environment is characterized by poverty and unemployment in the greater part of its communities. AI/AN poverty rates were over twice the general populations' in 1999. A study in 2000 illustrated that adult AI/AN males earned \$8200 less than the national male average; likewise, adult AI/AN women fell short by \$4400.

The Native American community's debilitating socioeconomic condition greatly detracts from its members' living conditions, diet, employment status, physical activity level, and overall health.

### *Psychosocial*

Research by Whitbeck et al. describes a "soul wound" among AI/AN populations; cross-generational historical trauma and grief layers over one's life span, negatively affecting emotional health and mental well-being. Largely, this trauma is attributed to the centuries of adversity AI/ANs have experienced in America. This adversity clearly persists, manifested as poor economic status, sense of cultural disconnection, and discrimination.

Additionally, no evidence yet suggests that the AI/AN cultural framework views obesity as a medical problem. Often, when over half of an AI/AN population experiences overweight/obesity, members adopt a normalization and resignation towards the issue. More so, a 1997 study concluded that Navajo adults over the age of 60 perceived moderate overweight to be healthy.

### *Physical Activity*

A 2005 National Institutes of Health (NIH) study disclosed that AI/AN adults are roughly 13% less likely to perform physical activity, compared to their White and Asian counterparts. Similarly, both the Strong Heart Study and Navajo Health and Nutrition survey revealed decreased levels of physical activity in reservation-residing AI/ANs between 45 and 74 years old. Specifically,

researchers identified safety concerns, lack of motivation/willpower, lack of time, and limited child care as barriers to activity.

## **Reducing Health Disparities Among American Indians**

Considering AI/ANs' exponentially-growing health disparities, developing more effective approaches to address public health and health care delivery in their communities is crucial. Current consensus points toward community-based strategies as a worthwhile starting point for such efforts; these strategies would emphasize tribal liaisons, and respect tribal culture.

## **Community-Based Strategies**

The positive effect of community-based lifestyle interventions for preventing chronic disease is well-documented. In the 1990's, research on community-based risk reduction projects showed that community based activities, such as exercise classes and cholesterol screenings, could increase the level of physical activity prevalence rate for screening tests in a community, all on a relatively modest budget. Previous community-based interventions in Native American populations in New Mexico have been effective at reducing weight and improving glycemic control when compared to a control group. Community-based interventions can also be cost effective. A study in the Netherlands found that intervention costs needed to prevent 1 new case of diabetes were 2,000-9,000 Euros for community-based interventions compared to 5,000-21,000 Euro for standard healthcare interventions. Successful programs in the past have emphasized cultural relevance, self-efficacy, and a reliance on the community-researcher relationship. Thus, any intervention targeting chronic diseases like obesity and diabetes within the Zuni community must be congruent with their traditional culture and values. In devising a procedure, input from tribal community members and leaders must be sourced, particularly due to their instrumental role in promoting lifestyle change.

## Identifying Cultural Barriers to Health Care in Zuni

Several barriers have been identified by the U.S. Commission on Civil Rights which play a role in NA/NI health disparities. These include discrimination, ethnic bias, racism, a paucity of culturally-competent care, and adverse environmental factors. Zuni Health Initiative (ZHI) interviews have demonstrated additional barriers. Structural barriers involve: 1) cost and inconvenience of transportation to/from doctors' appointments; 2) the transient nature of the communities healthcare provider workforce; 3) perception of misdiagnosis or late diagnosis of disease; 4) perception of health care rationing; 5) language barriers; 6) poor patient education. Psychological barriers comprise: 1) anxiety; 2) fear of diagnosis of chronic disease; 3) reluctance to practice self-care; 4) resistance to dietary modification; and, 5) resistance to periodic physical activity.

## Rationale

This research project aims to conduct an observational, qualitative and quantitative study, to evaluate the use of a novel chronic disease prevention approach for improving clinical outcomes and health-related quality of life in Zuni Indians with chronic disease. Our approach will attempt to address the factors leading to health disparities, as described in *Background*. Specifically, this multifaceted approach will assess the efficacy of a culturally sensitive, home-based diabetes prevention (HBDP) model, while determining which of the populations' perceptions are most prohibitive to chronic disease management. Zuni participants will have undergone prior baseline metabolic profile testing, completed a Patient Activation Measure (PAM) survey to determine patient engagement, and answered Educational Intervention Survey to gather more data on lifestyle factors. Essentially, our role is to hold periodic, informal classes for all participants about lifestyle modification measures, and diabetes pathophysiology. During these classes, we will measure participants' Hemoglobin A1C values, and provide each attendee an opportunity to deliberate over the results with us after class.

Along the same time frame, employees of the Zuni Health Initiative will perform lab work (for comparison of metabolic profiles to baseline values), and the PAM survey (for comparison to initial response). Finally, a three-month follow-up will take place, including both quantitative (blood/urine analysis, survey) values and qualitative (survey). Ultimately, this study will provide a highly-relevant assessment of the effectiveness of a community-based, culturally-sensitive HBDP model in addressing chronic disease.

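### A one-arm before-after study is said to assess efficacy and effectiveness, but without a comparator it can only estimate change from baseline, and the quality-of-life and prevention wording has no matching outcome

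*Protocol*

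**What the plan says.** The Rationale makes two causal promises. It opens with "Specifically, this multifaceted approach will assess the efficacy of a culturally sensitive, home-based diabetes prevention (HBDP) model" and closes by saying that "this study will provide a highly-relevant assessment of the effectiveness of a community-based, culturally-sensitive HBDP model" will result. It also describes the approach as one "for improving clinical outcomes and health-related quality of life in Zuni Indians with chronic disease".

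The design items are listed under Secondary Outcome Measures: "Number of arms: 1", enrolment of 60, a start in June 2012 and completion in December 2012. Of the participants it says: "They are all diabetics with HbA1c level of 6.6% and above". Methods likewise requires overt diabetes. The Abstract classes the study as an observational prospective cohort, yet names an educational intervention. The study itself delivers that intervention, as a class followed by monthly home visits.

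The outcomes are the PAM (primary) and HbA1c, glucose, lipids and BMI (secondary). Methods adds blood pressure. The Methods hypotheses are that PAM scores will rise and that the measures will improve on their own baseline values. Limitations and Biases covers the focus on diabetes, attrition and transfer to other populations. It does not mention the absence of a comparator.

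**The concern.** Efficacy and effectiveness are statements about what the intervention causes, relative to what would have happened without it. One arm with a baseline and one repeat measurement has no estimate of that second quantity. Four things could move the measures without any intervention effect:

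- **Regression to the mean.** Entry requires an HbA1c at or above a floor.
- **Season.** The study runs once, from June to December.
- **Usual care.** Treatment may change over six months.
- **Retest.** The same PAM questionnaire is answered twice.

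All of these enter the estimated change in full. A larger sample makes the confidence interval narrower around the mixture; it does not separate the parts.

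A significant change could then be presented as the efficacy assessment that the Rationale promises. In addition, a reader would look for a quality-of-life result that no listed outcome supplies, and for a prevention result that this population cannot supply.

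**Working it through.** **1. Claims against design**

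| Rationale wording | What the protocol provides | Match |
|---|---|---|
| Efficacy, effectiveness | One arm; change from own baseline (Methods); no control group or comparison series described | No |
| Health-related quality of life | PAM, HbA1c, glucose, lipids, BMI, blood pressure; the Educational Intervention Survey is described as demographics, self-management strategies and complications, and Methods does not list it among the items repeated at six months | No measure named |
| Diabetes prevention | All participants already diabetic; no onset or complication endpoint | No |
| Observational (Abstract, Rationale) | Class and monthly visits delivered by the study | No |

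**2. What the before-after difference estimates**

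Expected change = intervention effect + drift. With one arm there is one equation and two unknowns, so the effect is identified only if drift is assumed to be zero. The protocol neither states nor supports that assumption.

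**3. How often drift alone would be significant (illustration for HbA1c)**

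Inputs from Methods: n = 60; two-sided test; alpha 0.05, with Bonferroni over 8 measures giving 0.05/8 = 0.00625; clinically important difference 0.3.

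Assumed, not in the documents: a drift of 0.15 (half of 0.3) and zero intervention effect. The SD of the change is also assumed. Methods gives an SD of 0.5, but for HbA1c in normal subjects, so a range is shown. The middle value is 0.5 × √2 = 0.707, which is the SD of a difference between two uncorrelated readings that each have SD 0.5.

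For a paired t test with 59 degrees of freedom, the noncentrality is drift/SD × √60. The critical values are 2.001 (alpha 0.05) and 2.836 (alpha 0.00625).

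| SD of change | Noncentrality | Significant at 0.05 | Significant at 0.00625 |
|---|---|---|---|
| 0.5 | 0.15/0.5 × 7.746 = 2.324 | 63% | 31% |
| 0.707 | 0.15/0.707 × 7.746 = 1.643 | 37% | 13% |
| 1.0 | 0.15/1.0 × 7.746 = 1.162 | 21% | 5% |

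With a drift of 0.05 and SD 0.5 the figures are 12% and 2%. The probabilities therefore depend strongly on the assumptions. The bias in the estimate does not depend on the SD: it equals the drift.

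**4. Is drift of that order plausible?**

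The 6.6% entry floor gives one route. If a normal population with mean μ and SD σ is selected on the baseline reading being at least 6.6, and test-retest correlation is r, the expected fall is (1 − r) × σ × λ, where λ = φ(a)/(1 − Φ(a)) and a = (6.6 − μ)/σ.

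- μ = 7, σ = 2, r = 0.7: a = −0.2, λ = 0.675, fall = 0.3 × 2 × 0.675 = 0.41.
- μ = 8, σ = 1, r = 0.9: a = −1.4, λ = 0.163, fall = 0.1 × 1 × 0.163 = 0.02.

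Across μ 7 to 8, σ 1 to 2 and r 0.7 to 0.9, the fall is 0.02 to 0.41 points. All three ranges are assumptions. The upper end exceeds the 0.3 target. If eligibility rests on an earlier reading rather than the study baseline, less of this remains.

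**The case against.** The strongest reply is that the operative text is already modest. The Abstract speaks of associating the intervention with improvement, Methods calls the programme a pilot, and the hypotheses in Methods are about improvement on baseline. The single arm is declared openly, and a single-arm pilot is a legitimate design. All of this stands. It makes the document inconsistent with itself, but it does not remove the two causal claims in the Rationale or supply the missing limitation.

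Three stronger readings are tempting and are not supported:

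- **That a significant change will be reported as efficacy.** A reader might infer this from the Rationale. No analysis or reporting rule says so.
- **That prevention is a failed study aim.** The word works largely as a label for the model. The same section speaks of people who already have chronic disease, and onset of diabetes is nowhere an outcome. The wording misleads, but it is not an analysis that will fail. If preventing complications was meant, no such endpoint is set either.
- **That quality of life is definitely not measured.** The eight-page survey is only summarised, and the Rationale mentions a qualitative survey at follow-up whose content is not shown. What can be said is that no quality-of-life measure is named or listed as an outcome.

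A reader might also infer that stored data could remove the drift, since the Summary Description says: "In ZHI we also collected and stored clinical phenotype information and anthropological measurements from all participants". That sentence concerns participants in the Zuni Health Initiative. It does not say which of the present variables were stored, when, or by what assay. Subtracting an earlier rate of change would assume linear drift, comparable assays and stable treatment, and regression to the mean is not linear in time. No stored PAM is described, so the primary outcome would gain nothing.

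**Conclusion.** The point holds as a mismatch between claim and design. One arm measured before and after can estimate change from baseline to six months; it cannot assess efficacy or effectiveness, and the protocol does not acknowledge this. The quality-of-life aim has no named measure, the prevention label does not fit a population in which everyone has diabetes, and the observational label does not fit a delivered intervention. This conclusion rests on the text alone and needs no numerical assumption.

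The size of the bias cannot be determined from the documents. The 63% to 21% range (31% to 5% after Bonferroni) is conditional on the assumed 0.15-point drift and on an SD of change from 0.5 to 1.0. The upper figure should not be quoted alone, because it borrows an SD given for normal subjects. These figures concern HbA1c, a secondary outcome; the documents offer no basis for a matching figure on the PAM.

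**What to change.** 1. **Abstract and Rationale:** call the study a single-arm interventional before-after study.
2. **Rationale:** replace efficacy and effectiveness with change from baseline to six months in PAM and clinical indicators among people with diabetes. This agrees with the Abstract's language of association and the hypotheses in Methods.
3. **Rationale:** drop the quality-of-life aim, or name the measure that already captures it and list it as an outcome.
4. **Rationale:** describe the model as diabetes management rather than prevention.
5. **Limitations and Biases:** state that without a comparator the change cannot be attributed to the intervention, and name regression to the mean, season, usual-care changes and PAM retest as alternatives.
6. **Optional:** where earlier Zuni Health Initiative or Zuni Kidney Project values exist with known date and assay, show them descriptively beside the baseline-to-six-month change. Do not subtract them. People recruited by flier may have none.
7. **Any illustration of drift:** give it as a range over the assumed SD of change.

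Items 1 to 5 change wording only and need no new data, unless a quality-of-life measure has to be named. The price is a more modest conclusion.
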